**7.2.2 Cure :**

Assesment will be made at D21, in the final evaluation, using the following criteria

**Intubated patient :**

- Temperature  38° or  36.5°
- Leukocytes < 12000 / mm3

These 2 first criteria will not be used in the assessment if there is a documented extra-pulmonary infection.

- None purulent tracheal aspiration
- Chest X Ray normal or enhanced from D0 (decrease of the radiological score of at least 2 points)
- PaO2/FiO2  300 mmHg or improvment of more than 20% compared to D16.

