**5.2 Treatment**

All patients included in the study will be treated by a combination of antibiotics during the first 5 days (Beta-lactam + Aminoglycoside), then by monotherapy (Beta-lactam alone) for 3 or 10 days according to the group. The beta-lactam antibiotics will be administered in high doses during the first 3 days of treatment. Aminoglycosides will be administered as a single daily dose, with a loading dose administered on the first day of treatment. The patient will remain hospitalized (intensive care units or other units) for the duration of the treatment.

Definition :

- J0 = introduction of treatment whatever the time is
- J1 = first full day of treatment
- J4 = decrease in the dose of beta-lactam antibiotics, after 3 full days of treatment with high dose antibiotics; intermediate evaluation will be performed
- J6 = Stop aminoglycosides, after 5 full days of treatment
- J9 = Stop beta-lactam antibiotics in the "short" arm.
- J16 = Stop of the beta-lactam antibiotics in the "long" arm.
- J21 = Final evaluation.

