**7. Criteria of evaluation of the main objective**

**7.1 Parameters to define the clinical response :** highest temperature over 24 hours for hyperthermia or lowest in case of hypothermia ; leukocytosis (morning sample) character of bronchial secretions ; chest X-ray (radiological score: Appendix II) ; PaO2/FiO2 ratio (in a stable situation, outside intercurrent acute events)

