**Extubated patient :**

- Temperature  38° or  36.5°
- Leukocytes < 12000 / mm3

These 2 first criteria will not be used in the assessment if there is a documented extra-pulmonary infection.

- Absence of sputum or non-purulent sputum
- Chest X Ray normal or enhanced from D0 (decrease of the radiological score of at least 2 points)
- Ventilation on air or return to their previous level of oxygen requirement

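### For patients still intubated at D21, the 20% oxygenation gain needed for cure is measured from D16, an unexplained value taken after randomisation, whereas the X-ray in the same list is compared with D0

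*Protocol*

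**What the plan says.** Clinical response is the main criterion (Protocol, Section 7.2). Cure is judged once, at the final evaluation: "Assesment will be made at D21, in the final evaluation, using the following criteria".

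For a patient still intubated on that day, the oxygenation item asks for a PaO2/FiO2 of 300 mmHg or, as the alternative, an "improvment of more than 20% compared to D16". The comparison sign before 300 was lost when the text was extracted. The item directly above it has a different reference day: "Chest X Ray normal or enhanced from D0 (decrease of the radiological score of at least 2 points".

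Extubated patients have another oxygenation item, which does not mention D16: "Ventilation on air or return to their previous level of oxygen requirement".

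Section 5.2 fixes what D16 is: "J16 = Stop of the beta-lactam antibiotics in the" long arm. The short arm stops on J9. Section 8.3 has the allocated arm communicated by D5 at the latest. Section 7.1 names PaO2/FiO2 as a response parameter, to be measured in a stable situation, but sets no reference day for it. No section explains the choice of D16.

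**The concern.** A response criterion that measures improvement needs a reference that the compared treatments cannot have changed. D0 meets that need: both arms follow the same regimen until J9, so treatment duration cannot have influenced the D0 value. D16 does not meet it. By then the short arm has been off its beta-lactam for a week and the long arm is only just stopping. The reference can therefore carry an effect of the duration under test.

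The rule also measures something other than recovery from the pneumonia. It asks for a further gain over the last five days, gives no credit for improvement before D16, and can credit a partial rebound from a low D16 value.

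The item belongs to the primary endpoint. Section 11.2 accepts a difference of up to 10% between cure rates, which is 0.10 × 110 = 11 to 0.10 × 140 = 14 patients per group at the planned sizes. Misclassifying even a few patients unevenly would use up part of that margin.

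**Working it through.** The protocol states no figure to reproduce here. The check applies the written rule to example values.

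**Inputs**
- Rule as written (Section 7.2.2, intubated patient): item met if D21 ≥ 300 mmHg, or D21 > 1.20 × D16. Reading the lost sign as ≥ is an assumption.
- Alternative rule: item met if D21 ≥ 300 mmHg, or D21 > 1.20 × D0.
- Treatment stop days (Section 5.2): J9 short arm, J16 long arm. J and D are taken as the same day count, since J21 and D21 both denote the final evaluation.
- All PaO2/FiO2 values below are assumed. The protocol gives none.

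**Timing of the reference**
- Time off beta-lactam at D16: short arm 16 − 9 = 7 days; long arm 16 − 16 = 0 days.
- Time off beta-lactam at D21: short arm 21 − 9 = 12 days; long arm 21 − 16 = 5 days.

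**Example patients (mmHg)**

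| D0 | D16 | D21 | D21/D0 | D21/D16 | Item, D16 reference | Item, D0 reference |
|---|---|---|---|---|---|---|
| 150 | 240 | 270 | 1.80 | 1.125 | not met | met |
| 150 | 280 | 280 | 1.87 | 1.00 | not met | met |
| 150 | 320 | 320 | 2.13 | 1.00 | met (300 limb) | met (300 limb) |
| 180 | 180 | 180 | 1.00 | 1.00 | not met | not met |
| 220 | 120 | 150 | 0.68 | 1.25 | met | not met |

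The first row needs D21 above 1.20 × 240 = 288 and has 270. The last needs D21 above 1.20 × 120 = 144 and has 150.

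**What follows from the rule**
1. Improvement before D16 counts only if it brings D21 to 300. Since 1.20 × 250 = 300, the relative limb adds nothing to the absolute limb once D16 is 250 or more.
2. A patient below the D0 value at D21 can meet the item. This needs D21 > 1.20 × D16 and D21 < D0, so D16 < D0/1.20, about 83% of D0.
3. D16 alone can decide the result. With D0 = 150 and D21 = 270, the cut-off is 270/1.20 = 225: the item is met if D16 is below 225 and not met if it is 225 or higher.

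**The case against.** **D16 may be deliberate.** It is a scheduled interim evaluation of healing, and a late reference could be meant to detect relapse after treatment stops. That is possible, but the clause does not work that way. A relapse check would ask that oxygenation be maintained; this one demands a gain of more than 20%, so a stable patient below 300 fails. Nor is D16 a common end of treatment for both arms.

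**The 300 mmHg alternative protects most early recoveries.** This stands. A reader might infer that patients who recovered before D16 fail. The table shows otherwise: 150/320/320 passes. Only those below 300 at D21 without a further gain of more than 20% miss the item.

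**Meeting one item is not cure.** This also stands. The patient at 220/120/150 still needs non-purulent aspirate and an X-ray that is normal or at least 2 points better than D0. The temperature and leukocyte criteria apply too, unless an extra-pulmonary infection is documented. A failure under Section 7.2.1 after D3 carries forward to D21. The false-pass route is therefore narrow, though not closed: Section 7.2.1 lists no PaO2/FiO2 criterion by name.

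**The direction of bias is open.** A reader might infer that the rule favours 8 days, because a short-arm patient who dips after J9 has a low D16 reference. The opposite path is equally possible: a short-arm patient plateaus below 300 by D16 and fails, while a long-arm patient still improving after D16 passes. The protocol gives no trajectories by arm, so neither direction is supported.

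**D0 has a cost of its own.** With assumed values 150/280/185, D21 is 185/150 = 1.23 times D0, so the item is met under a D0 reference. Yet 185/280 = 0.66, a 34% fall since D16. The written rule would fail this patient. The point stands and is limited by the other cure and failure criteria.

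**Conclusion.** The concern holds in a limited form. In patients still intubated at D21, the relative oxygenation limb uses an unexplained value taken after randomisation, at a different time since the end of treatment in each arm, and at odds with the D0 reference for the X-ray. As written, it fails patients who improved by D16 but stay below 300 mmHg without a further gain of more than 20%. It also credits patients who worsened by D16 and partly rebounded.

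Misclassification can differ by arm. Its direction and its effect on the cure rates cannot be derived, because the protocol reports neither the proportion intubated at D21 nor the distribution of PaO2/FiO2. Extubated patients are not affected. The conclusion assumes that the lost sign means at or above 300 mmHg; the numerical examples rest on assumed values and show only what the rule permits.

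**What to change.** In Section 7.2.2, for intubated patients, make D0 the reference for the improvement of more than 20%, as for the X-ray, and leave the 300 mmHg alternative unchanged. The change should be made before outcomes are classified.

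It needs a one-word amendment and no new measurement: PaO2/FiO2 is on the daily follow-up sheet (Appendix VII), and the follow-up book is opened at pre-inclusion (Section 8.1).

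To cover the patient who falls back after D16 but remains more than 20% above D0, report a sensitivity analysis of cure with the D16 reference. If D16 was intended, the protocol should give the reason and explain how the comparison stays fair when the arms stop treatment 7 days apart.

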**Extubated patient :**

- Temperature  38° or  36.5°
- Leukocytes < 12000 / mm3

These 2 first criteria will not be used in the assessment if there is a documented extra-pulmonary infection.

- Absence of sputum or non-purulent sputum
- Chest X Ray normal or enhanced from D0 (decrease of the radiological score of at least 2 points)
- Ventilation on air or return to their previous level of oxygen requirement

**Home :**

The patient will be deemed cured at D21 if:

- 1. If data from the last day of hospitalization data is compatible with all the cure criteria
- 2. Absence of a new antibiotic treatment directed towards a lung infection (telephone interview at D21).

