**5.5** **Antibiotic adjustment**

If a new pulmonary or non pulmonary superinfection develops, all antibiotics are usable, supported by bacteriological data. Any change of antibiotic treatment for new pulmonary infection occurring after the beginning of the protocol has to be supported by a BAL if the patient is intubated.

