**7.2.1 Failure ;**

- Death for what ever reason during the protocol

- Initial clinical worsening judged after D3 of treatment:

septic shock (Appendix IV) or "sepsis syndrome" (Score of organ failure related to sepsis: SOFA Appendix V) without another documented infection - increase in the score of organ failure (increase in SOFA score by 2 points or more) with identification of the same microorganism at a new BAL

- Persistence or increase of all signs of pulmonary infection after D3 of treatment:

- temperature > 38.5° or < 36 °

- > 12000 WBC / mm3 or < 5000 / mm3

- purulent bronchial secretions

- absence of pulmonary radiological improvement and persistence of the original microorganism in the BAL

- A need to change the initial antibiotic for treatment intolerance (Appendix VI)

If failure is diagnosed, regardless of the day (After D3 of treatment), the patient is assessed as failure in the final evaluation at D21.

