**7.3 Intercurrent pulmonary infectious events**

Any intercurrent infectious event is documented by a new BAL. If a different bacteria is present at significant concentration, the patient is considered superinfected and is still evaluable at D21 ; if the BAL is sterile, treatment is continued and the patient will be evaluate at D21

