**11. Statistical design**

**11.1 Experimental design**

**It is a therapeutic trial of equivalence, with two parallel groups of which the main criterion is the rate of clinical cure at the end of treatment (D21).**

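### The primary endpoint scores a re-treated lung infection by where the patient is on D21, and both location and time for re-treatment depend on the arm

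*Protocol*

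**What the plan says.** Protocol section 11.1 describes an equivalence trial with "two parallel groups of which the main criterion is the rate of clinical cure at the end of treatment (D21"). Section 7.2.2 defines cure separately for three situations.

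- **Intubated:** temperature, leukocytes, secretions ("None purulent tracheal aspiration"), chest X-ray and PaO2/FiO2. There is no antibiotic item.
- **Extubated:** temperature, leukocytes, sputum, chest X-ray and oxygen need ("Ventilation on air or return to their previous level of oxygen requirement"). There is no antibiotic item.
- **Home:** data from the last hospital day must fit the cure criteria, and there must be "Absence of a new antibiotic treatment directed towards a lung infection (telephone interview at D21").

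Section 7.2.1 counts as failure: death; septic shock, sepsis syndrome or SOFA worsening as defined there; "Persistence or increase of all signs of pulmonary infection after D3 of treatment", a list that ends with "absence of pulmonary radiological improvement and persistence of the original microorganism in the BAL"; and a change of the initial antibiotic for intolerance. A failure diagnosed after D3 is carried forward to D21. A new antibiotic course for a lung infection is not on the list.

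Section 5.5 provides for re-treatment: "If a new pulmonary or non pulmonary superinfection develops, all antibiotics are usable". Section 7.3 says of a new pulmonary event: "If a different bacteria is present at significant concentration, the patient is considered superinfected and is still evaluable at D21". It also covers a sterile BAL, but not regrowth of the same organism.

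Section 5.2 stops the beta-lactam at J9 in the short arm and J16 in the long arm, and keeps patients in hospital for the whole course.

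**The concern.** Relapse that needs more antibiotics is the main efficacy risk of a shorter course, so the primary endpoint should score it the same way for everyone. As written, it rules out cure for a patient at home. In hospital it leaves no trace on the endpoint if the patient looks well again on D21 and never met the failure definition.

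Where a patient is on D21 is not independent of the assigned arm, because the course length sets the earliest discharge. The cure rate in each arm is then partly a product of the scoring rule, in a trial whose conclusion rests on a 10-point margin.

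**Working it through.** **1. The plan's own figure (context only).** Section 11.2 adopts a cure rate of 0.80 with 140 per group, 280 included and 350 pre-included. The column symbols are lost in the text at hand; I read 0.10 as one-sided alpha and 0.20 as beta. Then n = 2 × 0.80 × 0.20 × (1.2816 + 0.8416)² / 0.10² = 144.3, so 145 against the stated 140. Power at 140 is 79.1%, and 280 / 0.8 = 350 exactly. The plan's figure is adequately reproduced and is not in dispute.

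**2. The same event under each rule.** Take a recurrence after the end of treatment that is re-treated, does not meet the failure list, and leaves the patient clinically well on D21.

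| Situation | Rule that applies | Score |
| --- | --- | --- |
| Intubated on D21 | Clinical criteria only | Cure |
| Extubated, in hospital on D21 | Clinical criteria only | Cure |
| At home, re-treated after discharge | Clinical criteria plus no new antibiotic for lung infection | Not cured |
| Re-treated in hospital, then discharged | Unclear whether the telephone item covers it | Ambiguous |

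**3. How a hospital recurrence can miss the failure list.**

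- Section 4.1 diagnoses pneumonia on 2 of 3 clinical signs (with radiology and BAL), while the persistence rule in 7.2.1 asks for all signs. A two-sign recurrence can meet the entry definition and not the failure definition.
- Section 5.5 asks for a BAL before a change for new lung infection only if the patient is intubated. Without a BAL the original organism cannot be shown. Section 7.3 says any intercurrent event is documented by BAL, so the two sections need reconciling.
- Section 7.3 has no rule for the same organism. With a different organism the hospital patient stays evaluable, whereas the home item makes no distinction by organism.

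**4. Time available.** Short arm: 21 − 9 = 12 days. Long arm: 21 − 16 = 5 days. A short-arm relapse has up to 7 more days to appear, be re-treated and clear.

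**5. Direction.** In one arm let r be the proportion with a re-treated recurrence outside the failure list, h the share of these at home on D21 (all caught by the home item), and m the share of those in hospital who meet every clinical criterion on D21. The proportion scored as not cured because of recurrence is

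r × [h + (1 − h)(1 − m)] = r × [1 − (1 − h)m].

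- With everyone in hospital (h = 0) and equal m, the observed difference is (r_short − r_long)(1 − m), so a true difference shrinks. A larger m in the short arm, which the 12 versus 5 days makes plausible, shrinks it further.
- With equal r and equal m but more short-arm patients at home, the difference is r × m × (h_short − h_long) > 0. That is a spurious deficit in the short arm.

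The two effects have opposite signs, and the documents supply none of r, h or m.

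**6. Illustrations (all rates assumed, h = 0).**

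- 18% versus 6%, m = 0.7: 12 points seen as 0.12 × 0.3 = 3.6.
- 15% versus 5%, m = 0.6: 10 points seen as 0.10 × 0.4 = 4.
- 6% versus 3%, m = 0.3: 3 points seen as 0.03 × 0.7 = 2.1.

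**7. Effect on the conclusion, if masking dominates.** Assume the short arm is truly 10 points worse and a net x points of its relapses are scored as cures. On the risk-difference scale, P(conclude equivalence) = Φ(x / SE − z), where SE² = [p_L(1 − p_L) + p_S(1 − p_S)] / n and p_S = p_L − 0.10 + x. For the adopted row with x = 0.03: p_S = 0.73, SE = √[(0.16 + 0.1971) / 140] = 0.0505, and Φ(0.594 − 1.282) = 0.246.

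| Net points masked | 0 | 2 | 3 | 5 | 8 |
| --- | --- | --- | --- | --- | --- |
| 0.80, n = 140, alpha 0.10 | 10% | 19% | 25% | 39% | 64% |
| 0.90, n = 110, alpha 0.05 | 5% | 11% | 16% | 30% | 60% |

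If the home effect dominates, x is negative. The chance of a false conclusion then falls below alpha, but a short course that is truly equivalent is penalised.

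**The case against.** **The home item has a purpose.** Patients at home are not examined on D21, so the telephone question can stand in for a missing examination. That explains why an item was added at home. It does not explain why re-treatment, which is known for hospital patients, is ignored there.

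**The masking route is narrow.** Relapses with death, with shock or SOFA worsening as defined, or with all signs plus the original organism remain permanent failures. A masked relapse must also be re-treated and meet every clinical item by D21, including an X-ray that is normal or at least 2 points better than D0, within at most 12 days in the short arm. This stands: the gap does not hide every relapse. The layout of the 7.2.1 list also leaves some doubt about how the BAL clause attaches to the signs.

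**A reader might infer a one-way bias toward equivalence.** The documents do not support that. Section 5.2 allows short-arm discharge from about J9 and long-arm discharge only from about J16, so the stricter home rule falls more often on the short arm and works against it.

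**A reader might also take the 12-point difference seen as 3.6 as an estimate.** It is not one. The rates are assumed, every relapse is placed in hospital, and the 3-point case shrinks only to 2.1.

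**Superinfection was kept evaluable on purpose.** Section 7.3 says so, and superinfection is a separate secondary objective (10.1). A blanket rule failing every lung-directed antibiotic would override that choice and merge relapse with superinfection. This stands and limits the fix.

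**The failure and cure lists are not complementary, but this adds little.** The measure is the cure rate, so a patient who does not meet the cure criteria is already not a cure. One sentence is enough.

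**Conclusion.** The endpoint is inconsistent as written, in the primary definition that section 7.2 itself fixes: the same re-treated recurrence is not a cure at home and can be a cure in hospital. Location and the time for re-treatment before D21 both depend on the arm, so the inconsistency does not cancel between arms. No other section removes it.

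The net direction is uncertain and the size is unknown, because the documents give no relapse rate, no share at home and no rescue rate. The error probabilities above hold only if masking dominates, with a true deficit of exactly 10 points and the stated reading of the sample-size table. Under those assumptions a net 2 to 5 masked points takes the chance of a false equivalence conclusion from 10% to between 19% and 39%. This should be corrected because the trial's conclusion rests on this one outcome, not because a particular bias has been shown.

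**What to change.** Change the scoring only; nothing here concerns how a recurrence is treated.

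- Apply one rule to intubated, extubated and home patients: a new antibiotic course for recurrence of the initial lung infection (same organism, or no different organism documented) before D21 means not cured.
- State the period covered and make it the same in both arms. It should not begin at J9 without a reason, since the failure list already applies after D3. Say whether re-treatment in hospital followed by discharge is included.
- Score different-organism pulmonary superinfection the same way at home and in hospital, reconciling the home item in 7.2.2 with 7.3. Add a sensitivity analysis that counts it as non-cure.
- Reconcile sections 5.5 and 7.3 on when a BAL documents a new pulmonary event, because the scoring depends on it.
- State that any analysed randomised patient who does not meet all cure criteria at D21 is counted as not cured.

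The cost is wording: antibiotics, superinfection and BAL results are already on the daily follow-up sheet (Appendix VII), and the telephone interview already exists. The downside is that observed cure rates fall somewhat in both arms, so the 80 to 90% planning range in section 11.2 should be checked against the revised definition.

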**7.3 Intercurrent pulmonary infectious events**

Any intercurrent infectious event is documented by a new BAL. If a different bacteria is present at significant concentration, the patient is considered superinfected and is still evaluable at D21 ; if the BAL is sterile, treatment is continued and the patient will be evaluate at D21

**7.4 Non-pulmonary infectious intercurrents events**

Any modification of antibiotics will be preceded by the collection of bacteriological samples deemed necessary. If an intercurrent non-pulmonary Infection is documented, the patient is considered superinfected and remains evaluable at D21 on intention to treat.

**8 Conduct of test**

**8.1 Pre-inclusion**

Takes place on the day of completion of the BAL if the patient meets the criteria for inclusion (except bacteriological data). A follow-up book is then opened for the patient (daily monitoring sheet: annex VII)

